### 2.7. Assessments of pain

Different aspects of pain will be examined using self-reports and experimental pain paradigms (i.e., QST) to elicit and assess acute pain responses before and after acute stress, and during fMRI.

#### 2.7.1. Self-reported pain.

An overview of the pain-related trait questionnaires and timing of administration can be found in Table 1. A VAS involving a slider will be used to assess self-perceived pain intensity effects at baseline, and before and after the acute stress induction (i.e., pain intensity and pain unpleasantness). A range from zero to 100 will be used, with zero representing “no pain/unpleasantness at all”, and 100 representing “most pain/unpleasantness imaginable” [44]. The change in self-perceived pain intensity/ unpleasantness will be calculated by subtracting VAS-scores (Δ self-perceived pain = post-stressor VAS-scores – pre-stressor VAS-scores).

Pain origin, pain onset, last pain, pain evolution, pain pattern, pain throughout the day, pain quality, pain intensity, and pain location will be reported in the ten days prior to the start of the experiment or in the screening. Current pain intensity and pain location will be questioned on the day of the experiment itself.

#### 2.7.2. Quantitative Sensory Testing.

A static and dynamic QST battery will be used to assess pressure pain thresholds (PPTh), heat pain threshold (HPTh), heat pain tolerance (HPTo), conditioned pain modulation (CPM), and tonic temporal summation of pain (TSP).

To determine the presence of local and/or widespread hyperalgesia, PPTh will be assessed using a digital algometer with a one cm rubber tip (FDX50, Wagner Instruments, USA, Range 250 x 0.2N) on the following bilateral body sites locations: the proximal one-third of the calf, on the gastrocnemius muscle [54,55], five cm lateral to the third lumbar vertebra at the level of the lumbar vertebral column on the erector spinae muscle [54–56], and five cm distal to the lateral epicondyle of the humerus on the extensor carpi radialis muscle [54,57]. Each assessment will start at the left side, and the order of locations will be randomized. Participants will sit with 90° flexion in the knees, a neutral to slightly flexed low back position, and the forearms in a prone position with slight elbow flexion (30°), supported by a table. The pressure will be build up at one kilogram per second, applied perpendicular to the muscle fiber direction, and participants will verbally indicate when they first experience discomfort [58]. The PPTh measurement will be performed three times at each location, with a ten-second interval between consecutive measurements to prevent skin sensitization [59,60]. The first measurement will be used for familiarization and discarded from analysis. The average from the second and third measurement will be used to calculate the mean PPTh [58].

Pain sensitivity of heat stimuli will be evaluated using the TSA-2 with a three cm contact probe (Medoc Ltd.). Utilizing the principles of the Peltier element, the passage of a current through the device induces temperature changes, which are controlled by an active feedback system. Once the target temperature is reached, the temperature will be actively adjusted back to the baseline temperature (i.e., 35°C). The contact probe will be placed three cm distally from the elbow in the center of the volar part of the non-dominant forearm, and participants will be provided with a dual-button response device. The thermal stimulus will start at baseline temperature and will increase at a controlled rate of 0.3°C/s. The participants will be instructed to press the blue button when the temperature becomes unpleasant (HPTh), and to press the red button when the temperature becomes intolerable (HPTo). The HPTh and HPTo will be determined three times with an interstimulus interval of 30 seconds to avoid skin sensitization. The heat pain suprathreshold (HPSTh, which is the average of HPTh values and HPTo values [61]) will be used as stimulus intensity in the CPM and TSP test paradigms.

To assess central pain facilitation, a tonic TSP test paradigm will be executed. The three cm thermode (Medoc Ltd.) will be placed three cm distally from the elbow in the center of the volar part of the dominant forearm and will be secured to the testing site with a velcro strap. Temperature will rise from baseline and will reach HPSTh temperature in 1.25 seconds. Therefore, the rate of temperature increase will vary depending on the temperature corresponding to the HPSTh. The heat stimuli will be applied for 117.5 seconds, after which the temperature will reach baseline again in 1.25 seconds, resulting in a total duration of 120 seconds [61]. Pain intensity will be assessed at 1.25 (T1.25 sec), 5, 10, 20, 40, 60, 80, 100 and 118.75 (T118.75 sec) seconds on a verbal rating scale ranging from zero to 100 (zero = “no pain”; 100 = “most pain imaginable”) after showing a VAS [44].

To assess the dysfunction of descending pain inhibitory pathways, a parallel CPM paradigm will be conducted. Two three-by-three cm thermodes (Medoc Ltd.) will be positioned three cm distally from the elbow in the center of the volar part of the forearm, with one thermode (corresponding to the test stimulus) applied to the dominant side, and the other to the non-dominant side (corresponding to the conditioning stimulus). First, heat stimuli will be elicited on the dominant forearm. Starting from baseline, the HPSTh temperature will be reached in 1.25 seconds and will last for 7.5 seconds. This is the test stimulus (TS1). After an interstimulus interval of 45 seconds, temperature will increase on the non-dominant forearm, will reach the HPSTh temperature after 1.25 seconds, and will maintain for 22.5 seconds. This is the conditioning stimulus (CS). Fifteen seconds after the start of the CS, the TS will be applied again on the dominant forearm (TS2) [62]. Pain intensity for TS1 and TS2 will be assessed just before the temperature starts declining (at 8.75 sec) and for CS 15 seconds after application, using a verbal rating scale ranging from zero to 100 (zero = “no pain”; 100 = “most pain imaginable”) after showing a VAS [44]. The magnitude of CPM will be determined by subtracting the verbal rating score of the TS in the presence of the CS from the verbal rating score of the TS alone (Δ CPM = TS_2_ - TS_1_). A negative change score reflects an anti-nociceptive response, indicating effective CPM, whereas a positive change score suggests pronociceptive response and inefficient CPM [60].

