### 2.11. General hypotheses

It is hypothesized that the pain groups that vary in pain extent and duration will show distinct profiles of stress system functioning. We expect that individuals with chronic widespread pain (fibromyalgia) will exhibit the most pronounced dysregulation of the stress system, characterized by lower basal cortisol levels due to chronic HPA axis exhaustion, blunted acute stress reactivity, prolonged stress recovery, increased ANS dysfunction with elevated sympathetic tone and reduced parasympathetic reactivation, and greater alterations in cortico-limbic circuitry, which will be associated with amplified pain sensitivity and impaired pain inhibition. Individuals with chronic localized LBP are expected to exhibit moderately dysregulated stress responses, with a mix of heightened and blunted HPA axis reactivity depending on pain extent and duration, increased basal stress levels as reflected in higher cortisol concentrations compared to pain-free controls, mild-to-moderate disruptions in ANS regulation, potentially less severe than in fibromyalgia and associated with impaired pain modulation. Individuals with subacute localized LBP are expected to display a more intact but still altered stress response compared to chronic pain groups, with heightened stress reactivity but preserved recovery, and increased risk for pain chronification (i.e., pain persistence at the six month follow-up) if they exhibit persistent stress exposure, higher basal stress levels, blunted stress reactivity, slower recovery, stress-induced hyperalgesia, and/or alterations in cortico-limbic circuitry. Pain-free individuals are hypothesized to exhibit a balanced stress response, with adequate stress reactivity and efficient recovery from acute stress induction, and the effective endogenous pain modulation compared to all pain groups.

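### The CPM score is defined in words with the opposite sign to its own formula and interpretation, so efficient and impaired pain inhibition can be swapped

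*Protocol article*

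**What the plan says.** Section 2.7.2 (Quantitative Sensory Testing) of the protocol article describes a parallel CPM paradigm, intended to assess dysfunction of descending pain inhibition.

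- **First test stimulus.** Heat is applied to the dominant forearm before any conditioning: "This is the test stimulus (TS1").
- **Second test stimulus.** The conditioning stimulus (CS) is then applied to the other forearm, and the test stimulus is repeated: "Fifteen seconds after the start of the CS, the TS will be applied again on the dominant forearm (TS2").
- **Rating scale.** Both test stimuli are rated verbally from 0 to 100 ("zero = “no pain”; 100 = “most pain imaginable"), so a higher rating means more pain.
- **Score in words.** CPM magnitude is obtained by "subtracting the verbal rating score of the TS in the presence of the CS from the verbal rating score of the TS alone".
- **Score as a formula, in the same sentence.** "Δ CPM = TS_2_ - TS_1".
- **Interpretation, in the next sentence.** "A negative change score reflects an anti-nociceptive response, indicating effective CPM", while "a positive change score suggests pronociceptive response and inefficient CPM".

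Section 2.11 (General hypotheses) states expectations with a direction. For fibromyalgia, stress system dysregulation is described as something "which will be associated with amplified pain sensitivity and impaired pain inhibition". Impaired pain modulation is expected in chronic localized low back pain, and effective endogenous modulation in pain-free controls. Section 2.10 (Statistical analysis) plans group comparisons of the outcome measures and correlations between pain and stress measures.

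**The concern.** One sentence gives two definitions of the same outcome, and they have opposite signs. The interpretation that follows belongs to only one of them.

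The sign carries the meaning of this score. It decides whether a participant is described as inhibiting or facilitating pain, and whether a group difference supports or contradicts Section 2.11. CPM is the measure that the article assigns to descending inhibition, so a reversed score would have fibromyalgia patients with impaired inhibition appear to inhibit well, and controls appear to inhibit poorly. Each correlation between CPM and a stress marker would also change sign.

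The mistake would be hard to notice afterwards, because neither the size of an effect nor its two-sided p-value changes.

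**Working it through.** The plan gives no numerical CPM result to reproduce. The check is of signs, using the article's own definitions.

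**Inputs (all from Section 2.7.2)**

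- TS1 = rating of the test stimulus alone.
- TS2 = rating of the test stimulus in the presence of the CS. The timing confirms this. Counting from the start of the CS ramp, the CS holds its target until 1.25 + 22.5 = 23.75 s. The second test stimulus starts at 15 s and is rated 8.75 s later, at 15 + 8.75 = 23.75 s. It is therefore delivered and rated while the CS is still on.
- Scale: 0 to 100, higher = more pain.
- Reading rule: negative = effective CPM, positive = inefficient CPM.

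**Step 1: the words.** Subtracting A from B means B - A. Here A is the rating with the CS (TS2) and B is the rating of the stimulus alone (TS1). The words define TS1 - TS2.

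**Step 2: the formula.** The bracket defines TS2 - TS1 = -(TS1 - TS2). The two agree only when TS1 = TS2.

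**Step 3: which version fits the reading rule.** If conditioning inhibits pain, TS2 is lower than TS1. Then TS2 - TS1 is negative, which the rule calls effective CPM, as it should. TS1 - TS2 is positive, which the rule calls inefficient CPM. The rule fits only the formula.

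**Step 4: worked values.** The article gives no ratings, so these are assumed for illustration.

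| TS1 | TS2 | What happened | Words: TS1 - TS2 | Printed rule then says | Formula: TS2 - TS1 | Printed rule then says |
|---|---|---|---|---|---|---|
| 60 | 45 | pain inhibited | +15 | inefficient | -15 | effective |
| 60 | 40 | pain inhibited | +20 | inefficient | -20 | effective |
| 40 | 60 | pain facilitated | -20 | effective | +20 | inefficient |
| 50 | 50 | no change | 0 | neither | 0 | neither |

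**Step 5: effect on the analyses.** Let D = TS2 - TS1, so that the score by the words is -D.

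- Group contrast: mean(-D) in group a minus mean(-D) in group b = -[mean(D) in a - mean(D) in b]. The sign reverses and the absolute size does not change.
- Correlation with any stress measure S: corr(-D, S) = -corr(D, S). The sign reverses.
- The variance of -D equals the variance of D, so F statistics, absolute t statistics and two-sided p-values do not change.

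**The case against.** The strongest case on the other side is that this is a slip of word order whose intended meaning is plain.

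- The labelled formula and both halves of the interpretation agree, leaving only the prose out of line.
- The article's other change scores are later minus earlier: self-perceived stress and affect in Section 2.4.1, and self-perceived pain in Section 2.7.1. TS2 - TS1 follows that pattern.
- Harm requires someone to pass over the formula, code from the words, and then apply the interpretation that belongs to the formula. An analyst who used TS1 - TS2 throughout and read a positive score as inhibition would reach the right conclusions.
- TS1 and TS2 are rated separately, so if both ratings are kept, a wrong sign can be put right by multiplying by -1.
- CPM is one of five measures in the sensory testing battery, the sample size rests on the stress assessments, and Section 2.11 does not name a CPM score or its sign.

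All of this stands, and it limits the size of the problem: the intent can be recovered, the harm is conditional and the error is reversible. It does not remove the contradiction. The sentence is the operative scoring rule for the study's measure of descending inhibition, and following its words literally together with the printed interpretation gives reversed conclusions.

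**Conclusion.** The concern holds. The verbal definition of the CPM score has the opposite sign to the formula in the same sentence and to the interpretation in the next.

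For any participant with TS1 different from TS2, the two definitions differ in sign and agree in size. Scoring by the words and reading by the printed rule would reverse every individual label, every CPM group contrast and every CPM-stress association. Absolute effects, two-sided p-values, sample size and power are not affected.

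The conclusion about the text needs no assumption beyond the ordinary meaning of subtracting one quantity from another. The consequence depends on the score actually being coded from the words, and nothing in the article shows whether it was. The numerical ratings are illustrative only. That TS2 - TS1 is the intended score is an inference, well supported by the formula, the interpretation and the article's other change scores.

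**What to change.** Reverse the order of the two ratings in the sentence, so that it says the rating of the test stimulus alone (TS1) is subtracted from the rating of the test stimulus in the presence of the CS (TS2). Leave the formula TS2 - TS1 and the interpretation as they are. Words, formula and reading rule then agree: TS1 = 60 and TS2 = 40 give -20, effective CPM; TS1 = 40 and TS2 = 60 give +20, inefficient CPM.

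Run one such worked pair through the code that computes the score, and confirm that the dataset keeps TS1 and TS2 as separate variables so that the sign can be verified. If a separate analysis plan repeats the definition, align it too.

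The cost is one sentence and a short code check. No procedure, data collection or sample size changes. Section 2.1 expects initial results by 1 December 2026, and the check should be done before CPM is analysed.

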### 2.8. MRI of the brain

An overview of the MRI scanning procedure can be found in Fig 2. Before entering the MRI room, an MRI safety checklist will be filled out by the participant, and the researcher will check the presence of any contra-indications and the removal of metal objects. Images of the brain will be acquired with a three Tesla MAGNETOM Prisma Fit using a 64-channel head coil (Siemens, Erlangen, Germany) MRI Scanner at the Core Ghent Institute for functional and Metabolic Imaging (GIfMI) at Ghent University, Belgium. As part of standard practice, images are checked visually during scanning and scans will be repeated if necessary (e.g., due to movement or other artefacts). Visual stimuli and instructions will be presented to the participant on an MRI-proof 32 UHD BOLD-screen through a Python script, using PsychoPy packages [63]. The following scanning sequence will be used to evaluate brain structure and function: (1) localizers, (2) T1-weighted structural MRI, (3) Resting-State functional MRI (RS-fMRI), (4) task-based fMRI, (5) field map, (6) Diffusion-Weighted Imaging (DWI), and (7) multi-post labeling delay (PLD) pseudo-Continuous Arterial pin Labeling (pCASL). The set of localizer scans will be used to determine the correct orientation and positioning for the subsequent scans.

**Fig 2 pone.0324089.g002:**
[figure not shown]
Overview MRI scanning procedure. Neural measures include MP-RAGE (Magnetization Prepared-RApid Gradient Echo) anatomical data, RS-fMRI (Resting-State fMRI), two task-based fMRI acquisitions (pain induction and TSP [Temporal Summation of Pain]), HPSTh (heat pain suprathreshold), HPTh (heat pain threshold), DWI (Diffusion-Weighted Imaging) and pCASL (Pseudo-Continuous Arterial Spin Labeling).

T1-weighted anatomical data will be obtained through Magnetization Prepared-RApid Gradient Echo (MP-RAGE), with a repetition time (TR) of 2250 milliseconds (ms), echo time (TE) of 4.18 ms and a slice thickness of 1.00 millimeters (mm) to determine macro-structural properties of the gray matter (i.e., surface area, cortical thickness and volume). During this scan, participants will be able to practice using the fMRI trackball system (NAtA Technologies), which will be used for providing ratings during the task-based functional scans.

Both RS and task-based fMRI scans will be acquired through echo planar imaging with a multiband factor of 4, with a TR of 1070 ms, a TE of 31 ms and a slice thickness of 2.5 mm. 60 slices of 2.5 mm will be acquired with a flip angle of 52 degrees. This set of functional imaging will be followed by a field map to facilitate possible artifact corrections during postprocessing.

RS-fMRI scans will be performed to evaluate functional connectivity relating to pain processing. Participants will be instructed to focus on a fixation cross and to let the mind wander.

During the first task-based fMRI scans acute brain responses to painful heat stimuli and their anticipation will be captured. Each trial will first consist of an anticipation phase between four and six seconds, during which a cue is presented that signals either a more painful (red thermometer), less painful (orange thermometer), or unknown (neutral; empty thermometer) stimulus. Participants are instructed on the meaning of the cues beforehand. The cue will be followed by a heat stimulation period of ten seconds, at an intensity equal to either the HPTh or the HPSTh, which will be recalibrated when the participant takes place in the scanner. To elicit heat stimuli, a three-by-three cm MRI-proof thermode (Medoc Ltd.) will be placed through a waveguide and will be applied on the volar part of the forearm. The combination between cue and stimulation intensity is randomized between trials and four conditions will be tested: (A) neutral cue + HPTh; (B) neutral cue + HPSTh; (C) more-pain cue + HPTh and; (D) less-pain + HPTh. Conditions (A) and (B) will allow for investigating the brain’s response to heat pain, while conditions (C) and (D) will allow for investigating the effect of cues (anticipation) on pain processing. Each condition will be repeated six times, and three additional trials (more-pain cue + HPSTh) will be added to reinforce the suggestion that the more-pain cue is associated with a more painful stimulus, resulting in a total of 27 trials. During heat pain stimulation, participants are told to focus on a central shape presented in the center of the BOLD-screen, reminiscent of the cues presented just before to reduce the level of visual difference. After each stimulation phase, the participant is allotted four seconds to recall and rate the pain intensity between zero and 100 via the fMRI trackball system by scrolling through the slider component. Then, a fixation cross is presented for eight to ten seconds (jittered), allowing participants to rest before the next trial starts.

During the second task-based MRI scans, TSP will be evaluated in the same way as outside the MRI scanner as described in 5.2. However, the stimulus (of two minutes) will be repeated three times, with an interstimulus interval of 30 seconds, to prevent skin sensitization. The participant will once again fixate on the same shape as during the previously described stimuli, and on the fixation cross during the baseline phases. The method for scoring pain intensity is identical as during the previous task.

DWI scans will be acquired using multiband with a factor of three [64], a TR of 3200 ms, TE of 85 ms and a slice thickness of 2.0 mm. B0 and additional b-values of 1000 and 3000 s/mm^2^ will be used in 101 gradient directions. During DWI, participants are presented with a fixation cross. Afterwards, a scan will follow in the opposite phase encoding direction to facilitate corrections during postprocessing.

Multi-PLD pCASL will provide information on differences in brain perfusion. Max. labeling duration is 1800 ms and fifteen PLDs will be employed: 900 ms, 1200 ms, 1500 ms, 1700 ms, 1800 ms, 1900 ms, 2000 ms, 2100 ms, 2200 ms, 2300 ms, 2500 ms, 2800 ms, 3100 ms, 3400 ms, 3700 ms. These timepoints will allow for accurate perfusion mapping in controls without pain, while also providing a margin for possibly delayed responses in participants in pain [65]. These scans have a TR of 4400.0 ms, TE of 21.70 ms and a slice thickness of 4.0 mm. Participants are once again presented with a fixation cross during the pCASL scans. The total MRI scan will have a duration of approximately 55 minutes.

### 2.9. Pain recovery or persistence

The General Perceived Recovery (GPR) scale will be used to assess recovery or persistence of LBP. Patients will be dichotomized as (1) either being recovered at six-month follow-up based on pain intensity <2/10 indicated on a VAS, no pain-related disability indicated by a PDI score <14/70, and recovery indicated on a 11-point VAS whereby patients rate perceived recovery from −5 (vastly worse) to +5 (greatly improved), with zero corresponding to ‘no change’, rated on average over the past month, or (2) being non-recovered or persisting when not fulfilling these criteria, and since the duration exceeded six months, their MSK pain is considered chronic [24].

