**Aims:**

The primary aim of this study is to characterize stress system (dys)functioning (i.e., including basal levels, reactivity and recovery to acute stress, and chronic stress levels) in musculoskeletal pain groups with varying pain duration and extent, and to investigate the interaction between stress and pain at the psychosocial, (psycho)physiological and neural level. The secondary aim is to define the contribution of stress to pain trajectories, including chronification and recovery.

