### 2.10. Statistical analysis

A sample size calculation was performed using G*Power 3.1. A medium effect size was taken as a conservative omnibus estimation in relation to the stress assessments, based on previous studies. Large to very large effects have been observed for chronic stress [66] and basal cortisol levels [53]. Furthermore, acute stress inductions often failed to yield reliable cortisol responses, but medium to large effects have been observed for stress reactivity associations with self-reported pain responses [22].

Based on a one-way omnibus ANOVA (similar, but slightly more conservative than mixed linear models) with four groups, α of.05, desired power of.80, and a medium effect size of f = .30, 128 participants in total (n = 32 across four groups) are required. Accounting for corrupt or missing data, a sample of n = 35/group will be recruited. Additional sensitivity analyses were executed to calculate the observable effect size based on this sample in the longitudinal arm of the study (parameters: α = .05, power = .80, two groups, two measurements, correlation among repeated measures.2−.6; total sample n = 56 to account for 20% dropout/loss to follow-up). The calculation indicated that small to medium effects would be detectable (f = .17−.24) for within-between interactions in a repeated measures ANOVA.

The different outcome measures will be compared between participant groups and between different time points, using appropriate statistical tests (e.g., linear mixed model, ANOVA). Correlation analysis will be used to examine pain-stress interactions. For the longitudinal arm, analyses will focus on changes over time (i.e., baseline versus six-month follow-up), group comparisons based on pain status (i.e., recovered vs persisting) at follow-up, and interactions between changes over time in stress system functioning and the pain groups. At its core will be a linear mixed model analysis with ‘time’ as the within-subjects factor and ‘pain status group’ as the between-subjects factor. Post-hoc comparisons and adjustments for multiple comparisons will be made using Bonferroni-correction, unless more suitable post-hoc tests are identified. For all statistical tests, statistical significance will be accepted at an α of.05.

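### The core longitudinal analysis uses six-month pain only as a recovered/persisting label; a graded analysis of the pain scores should be pre-specified beside it

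*Protocol article*

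**What the plan says.** The secondary aim reads: "The secondary aim is to define the contribution of stress to pain trajectories, including chronification and recovery". Section 2.9 defines the outcome classes: "Patients will be dichotomized as (1) either being recovered at six-month follow-up based on pain intensity <2/10 indicated on a VAS". A recovered patient must also score below 14/70 on the PDI and indicate recovery on a scale from −5 to +5. Anyone who misses a criterion is persisting.

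For the longitudinal arm, section 2.10 plans to examine change over time, "group comparisons based on pain status (i.e., recovered vs persisting) at follow-up", and the interaction of the two. The core model is a linear mixed model with time within subjects and the two-level pain status between subjects.

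The sensitivity calculation assumes "two groups, two measurements, correlation among repeated measures.2−.6" and a "total sample n = 56 to account for 20% dropout/loss to follow-up". It concludes that "small to medium effects would be detectable (f = .17−.24) for within-between interactions in a repeated measures ANOVA".

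**The concern.** VAS intensity and PDI are graded scores, available at entry and at six months. The label keeps only whether a patient ends below both cuts and also indicates recovery. A patient who falls from VAS 8 and PDI 50 to VAS 2 and PDI 14 is classed with one who got worse, while VAS 1.9 and VAS 2.0 can fall in different classes. Because the cuts are the complement of the entry thresholds in section 2.2, a patient who entered just above them needs only a small change to pass on VAS and PDI.

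The longitudinal sample is small and fixed. If stress functioning relates to pain course in a graded way, an analysis that sees only the label discards part of that information. A null result on the contribution of stress to chronification could then partly reflect the cut.

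**Working it through.** **Inputs from section 2.10.** Two groups, two measurements, correlation ρ from .2 to .6, and power .80; "statistical significance will be accepted at an α of.05". Two localized-pain groups of 35 give 70 patients, and 20% loss leaves 70 × 0.8 = 56.

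**Assumptions, not in the documents.** The recovered share p (range 10% to 50%); a normal pain score; a linear relation of a stress measure to that score.

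**Step 1: the plan's own figure.** For the within-between interaction, λ = f² × N × 2/(1 − ρ), with 1 and 54 degrees of freedom.
- f = .24, ρ = .2: λ = .0576 × 112/.8 = 8.06, power 79.6%.
- f = .17, ρ = .6: λ = .0289 × 112/.4 = 8.09, power 79.8%.

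Exactly 80% power needs λ = 8.14, that is f = .241 and .170. The stated range reproduces for a two-group comparison.

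**Step 2: what cutting a normal score does.** λ = 8.14 with N = 56 corresponds to r² = 8.14/(8.14 + 56) = .127, so r = .356. Cutting a normal score at proportion p multiplies its correlation with another variable by k = φ(z_p)/√(p(1 − p)). The values of k² are .637 (p = .5), .622 (.4), .576 (.3), .490 (.2) and .342 (.1). Power then follows from λ = 56 × r²/(1 − r²).

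**Step 3: label against graded score, linear relation, N = 56.**

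| Recovered share | Label power when graded = 80% | Graded power when label = 80% |
|---|---|---|
| 50% | 58.7% | 95.6% |
| 40% | 57.6% | 96.1% |
| 30% | 54.1% | 97.4% |
| 20% | 47.3% | 99.1% |
| 10% | 34.7% | nearly 100% |

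At an even split the label costs 80 − 58.7 = 21 points on the first reading and 95.6 − 80 = 16 points on the second. With the association held at the uncut r of .356/.798 = .446 (graded power 95.6%), label power is 80% at p = .5, 79% at .4, 75% at .3 and 68% at .2.

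Simulating an all-three-criteria label gave losses of 19 to 25 points against the mean of VAS and PDI, and 23 to 45 points against the mean of all three scores. Against VAS alone the loss was 6 to 19 points. These runs need an invented cut on the perceived-recovery scale, for which section 2.9 gives no number, so they are supporting evidence only.

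**Step 4: when the relation is not linear.** If stress differs only across the threshold, the label has about 80% power against 58% for the graded score (even split), or 79% against 53% (30% recovered). For mixtures at r = .40 and an even split, label against graded power was:
- purely linear: 69% v 88%
- equal weights of linear and step: 84.5% v 84.5%
- three-quarters step: 88% v 78%

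A floor effect, with observed scores floored 0.3 SD below the cut, reduced the linear-case gain from 19 to 11 points.

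**Limit.** These figures treat one stress measure and one pain score. With baseline pain as covariate, r becomes a partial correlation and one more degree of freedom is used.

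**The case against.** The strongest reply is that the label is the question. The abstract's methods describe the trajectories as recovery or persistence, and section 2.11 equates chronification with persistence at six months. The VAS and PDI cuts are the exact complement of the entry criteria and carry the same citation. The stress measures, which are the dependent variables, remain continuous. All of this stands, and it rules out several stronger readings that a reader might infer:

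- *The cut has no basis.* The cut-points have a visible one. What is missing is a reason for confining the core model to them.
- *The power statement is wrong.* It is correct for the two-group comparison it describes. The loss exists only relative to a graded alternative.
- *The loss is unconditional.* It reverses under a step relation, and the documents fix neither the shape nor the recovered share.
- *The graded scores will never be analysed.* Section 2.10 also plans correlation analysis of pain and stress, and does not limit it to baseline. It names no six-month score either, so the article neither shows nor excludes such an analysis.
- *The core model should be replaced.* A graded score answers a somewhat different question from recovered versus persisting. Putting the raw six-month score in place of the label in the mixed model would treat a fall from VAS 8 to 2 like an unchanged VAS of 2.

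It can also be said that a condensed article leaves supplementary models to a fuller plan. That limits the point to a request for pre-specification. It does not remove it, because the article does state its core longitudinal analysis, and that analysis rests on the label alone.

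**Conclusion.** The point holds in a limited form. The core longitudinal analysis uses six-month pain only through the recovered/persisting label, although VAS intensity and PDI are available as graded scores at both visits. With 56 patients, a linear relation and normal scores, this costs about 16 to 21 points of power at an even split, and typically more at uneven splits for a fixed association. The figure comes from those assumptions and not from the documents; near an equal mixture of linear and step relations the two analyses tie, and beyond it the label wins. Since the shape is unknown in advance, having both analyses pre-specified protects the secondary aim better than either alone. The graded regression also runs in the direction of the section 2.11 hypothesis, from stress features at baseline to later pain.

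**What to change.** In section 2.10, keep the mixed model with time and pain status, and keep the section 2.9 label as the clinical definition. Pre-specify beside it a graded analysis: regress six-month pain on the baseline stress measures (level, reactivity, recovery), with the baseline value of the same pain score as covariate. State in advance whether VAS intensity and PDI are analysed separately or as a standardised mean. If a graded time-interaction model is also fitted, use six-month pain adjusted for baseline pain, not the raw six-month score.

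The cost is one more pre-specified model, a check for linearity and floor effects, and a multiplicity rule that covers the label-based and graded analyses together. A slope is less immediately readable than two classes, but the label result is still reported. No new data are needed.
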